### Recruitment, randomisation and treatment allocation

Patients are recruited at UK hospitals with specialist melanoma oncology teams. Patient registration occurs at any point from the start of anti-PD-1 therapy up until 1 year (+ 4 weeks).

Randomisation occurs at 1 year (+/− 4 weeks) post start of anti-PD-1 therapy in eligible patients. Treatment allocation via a central automated 24-h system (provided by University of Leeds), using a 1:1 ratio is by minimisation, with a random element, stratifying for BRAF status (wildtype, mutant, unknown), prior use of BRAF/MEK inhibitor therapy for advanced melanoma (yes, no), prior use of (neo)adjuvant immunotherapy (yes, no), disease stage at start of anti-PD-1 treatment (unresectable stage III or stage IV disease), brain metastases (yes, no), ECOG performance status (0/1, 2), centre, treatment received within the previous 1 year (ipilimumab-nivolumab, nivolumab or pembrolizumab) and response after the first 1 year of therapy defined according to RECIST v1.1 criteria [23] (CR, PR, SD). No attempt at allocation concealment will occur due to practicalities of treatment within arms.

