### Sample size

Sample size calculations are based on the primary time-point of 2-year PFS, which is equivalent to 1 year post randomisation. To inform these calculations, data from CheckMate 067 was used which showed 43% and 37% of patients were alive and progression free at 1 year and 2 years after the start of treatment respectively in the nivolumab only arm, and 50% and 43% of patients alive and progression free at 1 year and 2 years for those receiving combination therapy [24]. This correlates with a relative reduction in PFS of 14% from 1 year to 2 years. Given that 100% of the DANTE randomised population will be alive and progression free at 1 year after starting anti-PD-1 therapy (i.e. at the point of randomisation), it is estimated that approximately 86% will be alive and progression free at 2 years on standard treatment (as used in CheckMate 067 [24]). Defining non-inferiority as a reduction in 2 year PFS of no more than 6%, with 80% power and a one-sided significance level of 5%, and accounting for a 5% drop out rate, 1208 patients (604 per arm) are required in total to test for this degree of non-inferiority using a one-sided log-rank test. Consensus for the non-inferiority margin was reached after discussions within the National Cancer Research Institute (NCRI) Skin Cancer Clinical Studies Group and patient representatives.

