Interpretation of non-inferiority for the primary endpoint of PFS will be based on the 90% (one sided type I error rate of 5%) confidence interval (CI) of the difference in PFS rates at 1 year post randomisation determined from Kaplan-Meier estimates at this time-point; the upper limit of the 90% CI will be compared with the non-inferiority margin of 6%. If it is below this margin then time-limited treatment will be declared as non-inferior to standard treatment. If the upper limit is above the non-inferiority margin then non-inferiority will not have been demonstrated. PFS and OS will be assessed using Kaplan-Meier curves. If appropriate, Cox’s Proportional Hazards model, adjusting for the minimisation factors, will be used to compare PFS and OS between the treatment groups. In addition, a sensitivity analysis of the primary endpoint will assess time to progression, where deaths without documented evidence of progression will be considered a competing-risk event. Time to progression will be investigated using cumulative incidence function curves and compared using Cox’s Proportional Hazards model if appropriate, to adjust for the minimisation factors.

The main QoL outcome of interest is the summary score of the EORTC QLQ-C30 [29]. Quality of life will be summarised at each time point using adjusted for baseline mean scores and 95% CIs. Summaries and differences between arms will be obtained and compared using a multi-level repeated measures model, allowing for time, treatment, and treatment-time interactions, and adjusting for baseline QoL and the minimisation factors (fixed effects) and participant and participant-time interaction (random effects) where appropriate, assuming missing data at random. Missing data patterns will be examined and alternative analyses using different missing data assumptions will be performed if appropriate (e.g. pattern mixture multi-level models). This methodology will be repeated to analyse scores from the EORTC QLQ-MEL38 [26].

Differences in response (defined by RECIST v1.1 criteria [23]) rates between the treatment groups will be compared using logistic regression for objective response and ordered logistic regression for best tumour response, adjusting for the minimisation factors. Sensitivity analyses will be conducted to allow for any deaths from causes other than melanoma, for whom no response status was observed. Both ITT and per-protocol analyses will be performed on the RECIST evaluable population.

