The Dutch Safe Stop Trial (Safe Stop-T, NTR7502 [39]) is an observational study of the STOP & GO strategy of PD-1 blockade where treatment is stopped within 4 weeks of confirmation of radiological response (CR or PR according to RECIST v1.1 criteria [23]). Radiological monitoring continues every 12 weeks with treatment immediately re-commenced in the event of progression. The primary outcome measure is the rate of ongoing response according to RECIST v1.1 criteria [23] at 2 years after the start of PD-1 blockade. Further sub-studies include Safe Stop-QoL which evaluates the impact of this early discontinuation of treatment on patient reported disease specific and generic health-related QoL, patient productivity and informal care resource use. Safe Stop-T [39] therefore aims to provide observational data on the safety of intermittent treatment in a cohort of 200 patients rather than identify the optimal duration of treatment through a randomised trial.

A cohort study [40] in 185 patients with advanced melanoma, across various treatment centres, who electively stopped anti-PD-1 therapy in the absence of progressive disease or treatment-limiting toxicity, provides further observational data on the impact of early discontinuation of anti-PD-1 treatment. In this study patients who experienced a best objective response (BOR) of CR during treatment (117 of 185) had a shorter median duration of anti-PD-1 therapy (11 months) and were significantly less like to experience PD following treatment discontinuation compared to those who experienced a BOR of PR (HR 2.99, 95% CI 1.45–6.16) or a BOR of SD (HR 5.15, 95% CI 2.19–12.09) [40]. This supports previously observed data that durable responses can continue in patients who discontinue treatment earlier than a planned duration of 2 years (as used in KEYNOTE-006 [20] and across many worldwide healthcare settings). The observed difference in PD across the subgroups of BOR poses the question of whether response during treatment should be considered when decisions on duration of anti-PD-1 therapy are made on an individual patient basis. Future prospective studies to answer this question are however required.

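### The crude Kaplan-Meier difference that decides non-inferiority uses none of the minimisation factors, so its interval is slightly conservative; an adjusted difference on the same 6-point scale would be a cheap improvement

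*Protocol article*

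**What the plan says.** Under *Recruitment, randomisation and treatment allocation*, the protocol article allocates 1:1 by minimisation with a random element. There are nine factors: BRAF status, prior BRAF/MEK inhibitor, prior (neo)adjuvant immunotherapy, stage, brain metastases, ECOG status, centre, treatment received, and "response after the first 1 year of therapy defined according to RECIST v1.1 criteria [23] (CR, PR, SD").

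Under *Statistical methods and analysis*, non-inferiority rests on the 90% interval for the difference in PFS rates at 1 year after randomisation, "determined from Kaplan-Meier estimates at this time-point; the upper limit of the 90% CI will be compared with the non-inferiority margin of 6" percentage points. No factor is named for this interval. A Cox model for PFS adjusted for the minimisation factors is also planned, but only if appropriate and with no decision rule. The stage 3 Cox model, the quality-of-life model, the response models and the duration-of-response model are all adjusted for these factors.

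Under *Sample size*, "it is estimated that approximately 86% will be alive and progression free at 2 years on standard treatment", and 1208 patients are required "to test for this degree of non-inferiority using a one-sided log-rank test". No covariate adjustment is mentioned there.

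**The concern.** Minimisation makes the arms more alike on prognosis than simple randomisation would. The sampling variation of the difference between arms then shrinks, but a standard error computed separately in each arm and added, as is usual for a Kaplan-Meier difference, does not reflect this. If the factors predict outcome, the nominal 90% interval over-covers, the true one-sided error falls below 5%, and some power is forgone.

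The document itself gives reason to think that one factor is prognostic. In its Discussion, patients who stopped treatment were less likely to progress after a complete response (CR) than those who "experienced a BOR of PR (HR 2.99, 95% CI 1.45–6.16) or a BOR of SD (HR 5.15, 95% CI 2.19–12.09"), for partial response (PR) and stable disease (SD) respectively.

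The planned adjusted analysis of PFS does not fill the gap. It yields a hazard ratio, which cannot be read directly against a margin in percentage points.

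**Working it through.** **Inputs from the protocol article.** Control PFS at 1 year after randomisation is 86%. The margin is 6 points ("Defining non-inferiority as a reduction in 2 year PFS of no more than 6"%). The design is set "with 80% power and a one-sided significance level of 5"%, "accounting for a 5% drop out rate, 1208 patients (604 per arm) are required in total". The hazard ratios of progression against CR are 2.99 (PR) and 5.15 (SD), with limits 1.45–6.16 and 2.19–12.09.

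**Assumptions.** The response mix of the randomised patients is not given, so a CR share of 20–63% is used; 63% is the share in the cited cohort (117 of 185). The PR/SD split is also assumed. Balance on response is taken as near-exact, and the usual unadjusted variance is assumed.

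**1. The plan's sample size.**
- Hazard ratio at the margin: ln 0.80 / ln 0.86 = 1.4795.
- Schoenfeld events: 4 × (1.645 + 0.842)² / (ln 1.4795)² ≈ 161.2, rounded up to 162.
- At the control event rate in both arms: 162 / 0.14 = 1157. With 5% drop-out: 1157 / 0.95 = 1218, or about 1212 without rounding the events up.

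This is within 1% of 1208, so the plan's figure is reproduced as an unadjusted log-rank calculation.

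**2. What the crude difference rule delivers at that size.**
- After 5% drop-out, 604 × 0.95 ≈ 574 per arm.
- SE = √(2 × 0.86 × 0.14 / 574) = 0.02048. The half-width is 1.645 × 0.02048 = 3.37 points.
- Power at equal true rates: Φ(0.06 / 0.02048 − 1.645) = 90.0%.
- For 80% power this rule needs 414 per arm: 828 / 0.95 ≈ 872 in total.

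**3. Variance explained by response.** The CR hazard is solved so that the mixture gives 86% at 1 year. Then R² = between-group variance / (0.86 × 0.14), and the one-sided error of the crude rule is 1 − Φ(1.645 / √(1 − R²)).

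| CR/PR/SD (assumed) | R² | One-sided error |
|---|---|---|
| 63/24/13% | 0.070 | 4.4% |
| 35/45/20% | 0.043 | 4.6% |
| 25/50/25% | 0.034 | 4.7% |
| 20/50/30% | 0.029 | 4.75% |

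Across the confidence limits of the hazard ratios, and over the mixes tried, R² runs from about 0.01 to 0.15.

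**4. Simulation of crude against response-standardised intervals.** This used 574 per arm, a binary 1-year outcome, no censoring and exact balance on response only.

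| Mix, cited hazard ratios | Half-width (points) | Power | Crude one-sided error |
|---|---|---|---|
| 30/50/20% | 3.36 → 3.30 | 90.6% → 91.1% | 4.7% |
| 63/25/12% | 3.37 → 3.24 | 90.8% → 91.8% | 4.3% |

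Across the hazard-ratio limits, the crude error was 3.5–4.9% and the power gain 0.3–2.1 points. The standardised interval stayed at 4.8–5.2%.

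The closed form agrees. Under balance, crude power is Φ((0.06/SE − 1.645)/√(1 − R²)) and adjusted power is Φ(0.06/(SE√(1 − R²)) − 1.645). At R² = 0.037 these are 90.5% and 91.0%; at R² = 0.069 they are 90.8% and 91.8%.

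**The case against.** The strongest reply is that nothing here is invalid. The crude difference is on the scale of the margin, needs no model, and errs towards not declaring non-inferiority, which is the safer side when the question is whether treatment can be stopped. That stands: no false claim of non-inferiority becomes more likely.

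A reader might infer that the trial throws away power it has paid for. The documents do not support this. The sample size bought 80% for an unadjusted log-rank test, and the crude rule gives about 90% at that number. Adjustment would add an unbudgeted gain.

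The inputs are also soft. The hazard ratios come from an observational cohort of 185 patients who all stopped treatment. They concern best objective response and later progression, whereas the trial minimises on response after the first year and counts PFS events in both arms. Their limits are wide, and at the lower limits the gain almost vanishes. Minimisation with a random element over nine factors balances response only approximately, so for given inputs these figures show the most that response alone could do. The other factors may add to the effect, but the document gives no figures for them. The variance formula is not stated either, and may be settled in an SAP that is not shown.

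Finally, a model-based primary analysis has a price. About 0.14 × 1148 ≈ 161 events must carry nine factors including centre, and the plan itself treats proportional hazards as uncertain. This argues for a sparing adjustment that does not rest on proportional hazards. It does not argue against adjusting.

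**Conclusion.** The point holds as a modest matter of efficiency and consistency. The deciding interval uses none of the factors on which patients were allocated, unlike the plan's other main modelled comparisons, and the adjusted hazard ratio beside it cannot be set directly against the margin.

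Under the assumptions above, the one-sided error is about 4.4–4.75% at the cited hazard ratios. The power forgone is about 0.5–1 point there, and up to about 2 points at their upper limits. It is neither a validity fault nor a failure to reach the planned power.

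The case for acting is that the remedy is cheap. There is also a secondary reason. The plan gives the per-protocol analysis equal weight, and exclusions after randomisation can undo the balance that minimisation created. Adjustment would then limit bias from measured imbalance as well as improve precision.

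**What to change.** Pre-specify as the deciding analysis a covariate-adjusted difference in 1-year PFS, with its 90% interval compared with the same 6-point margin, in both the ITT and per-protocol populations. Suitable methods are Kaplan-Meier estimates standardised over response, pseudo-value regression, or g-computation from a model that does not assume proportional hazards for treatment.

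Adjust for response at 1 year and the other key patient-level minimisation factors. Handle centre sparingly, given roughly 160 events. Fix the covariate list and the variance method before the primary analysis. Keep the crude Kaplan-Meier difference as a supporting analysis.

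The cost is SAP wording, some programming and modest model dependence. The factors are already recorded at randomisation, and neither the margin nor the 1208 changes.

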### Trial organisation and administration

The Clinical Trials Unit, on behalf of the trial sponsor, ensure the trial is undertaken according to the principles of Good Clinical Practice (GCP) and in line with the relevant UK Research Governance Frameworks. Trial registration is ISRCTN15837212 and the EudraCT number is 2017–002435-42.

An independent Data Monitoring and Ethics Committee (DMEC) review the safety and the ethics of the trial with detailed unblinded interim reports submitted at least annually. The DMEC, together with the Trial Steering Committee (TSC) and the funder are responsible for enacting stop/ continuation rules during the interim stages (stages 1 to 3) if predefined targets for patient recruitment or efficacy are not met.

### Sub-studies

To inform trial recruitment both now and in the future, an integrated qualitative sub-study is included. This sub-study will explore patients’ views on decision making with regard to trial entry and subsequent randomisation. A semi-structured topic guide facilitated exploration will be undertaken for 24 patients eligible for registration (6 patients) or randomisation (18 patients, 2:1 ratio of randomised to non-randomised patients). All interviews will be audio recorded following informed consent and a thematic analysis [35] will be performed.

At recruitment, patients consent will be sought to provide access to any archival melanoma tumour samples, to be used in future translational research.

The trial protocol and this paper have been written in accordance with standard protocol items: recommendations for interventional trials (SPIRIT) guidelines [36]. A SPIRIT checklist is included as supplementary material (Additional file 2: Table S2).

## Discussion

Given the implications to both patients and health care systems across the world, there is a high international imperative to define optimal duration of therapy with anti-PD-1 antibodies. Treatment-associated burden to patients includes time, financial and potential drug induced toxicity whereas treatment-associated burden to healthcare includes capacity, drug costs and associated treatment delivery costs. DANTE hopes to answer the question as to whether continued treatment is justified accounting for these costs or if time-limited treatment can provide greater value without loss of treatment benefit.

To date, a single randomised trial, CheckMate 153, has reported only exploratory data on the optimal duration of anti-PD-1 treatment. This trial randomised patients with advanced non-small cell lung cancer to continuous and time-limited (1 year) nivolumab treatment to evaluate the incidence of high-grade select treatment AEs [37]. In this exploratory analysis, median overall survival was not reached for continuous treatment and was 23.2 months for time-limited treatment [37]. The 1 year OS rate was not statistically different between the two groups (88% for continuous treatment vs. 81% for time-limited treatment with a HR = 0.63, 95% CI 0.33–1.20) [37]. In this study of 1375 patients, only 15% (*n* = 218) remained on nivolumab at 1 year and so the number of patients eligible for randomisation was small [37]. It is also arguable that due to different immunosensitivities of different tumour types, the results are not generalisable.

Two additional clinical trials are ongoing in metastatic / unresectable melanoma to evaluate the impact of stopping treatment in patients upon achieving response: STOP-GAP and Safe Stop-T.

The Canadian STOP-GAP study (NCT02821013) [38], is a phase 3 trial which randomises eligible patients within 16 weeks of starting anti-PD-1 therapy to standard treatment of 2 years or to treatment until maximal tumour response (defined by at least 2 radiological measurements 3 months apart) with re-treatment at time of progression. STOP-GAP, designed to complete recruitment at the end of 2023, therefore primarily aims to evaluate the role of re-challenge rather than the specific question of optimal treatment duration.

The Dutch Safe Stop Trial (Safe Stop-T, NTR7502 [39]) is an observational study of the STOP & GO strategy of PD-1 blockade where treatment is stopped within 4 weeks of confirmation of radiological response (CR or PR according to RECIST v1.1 criteria [23]). Radiological monitoring continues every 12 weeks with treatment immediately re-commenced in the event of progression. The primary outcome measure is the rate of ongoing response according to RECIST v1.1 criteria [23] at 2 years after the start of PD-1 blockade. Further sub-studies include Safe Stop-QoL which evaluates the impact of this early discontinuation of treatment on patient reported disease specific and generic health-related QoL, patient productivity and informal care resource use. Safe Stop-T [39] therefore aims to provide observational data on the safety of intermittent treatment in a cohort of 200 patients rather than identify the optimal duration of treatment through a randomised trial.

A cohort study [40] in 185 patients with advanced melanoma, across various treatment centres, who electively stopped anti-PD-1 therapy in the absence of progressive disease or treatment-limiting toxicity, provides further observational data on the impact of early discontinuation of anti-PD-1 treatment. In this study patients who experienced a best objective response (BOR) of CR during treatment (117 of 185) had a shorter median duration of anti-PD-1 therapy (11 months) and were significantly less like to experience PD following treatment discontinuation compared to those who experienced a BOR of PR (HR 2.99, 95% CI 1.45–6.16) or a BOR of SD (HR 5.15, 95% CI 2.19–12.09) [40]. This supports previously observed data that durable responses can continue in patients who discontinue treatment earlier than a planned duration of 2 years (as used in KEYNOTE-006 [20] and across many worldwide healthcare settings). The observed difference in PD across the subgroups of BOR poses the question of whether response during treatment should be considered when decisions on duration of anti-PD-1 therapy are made on an individual patient basis. Future prospective studies to answer this question are however required.

The DANTE trial will help define what constitutes the optimal duration of anti-PD-1 therapy in the treatment of advanced melanoma. Designed as a prospective randomised controlled trial it will assess whether treatment should be continued for a set time and specifically whether this should for a reduced duration of 1 year. This contrasts with STOP-GAP [38] and Safe Stop-T [39] which will assess whether treatment should be continued to a set response. All three trials are however key to expanding the evidence base and ensuring patients receive the correct duration of treatment, both in terms of efficacy and costs, without being given too much or too little.

The outcomes of these studies will not only enable better patient and clinician decision making on an individual patient basis but ensure that continuation of these high cost treatments remain appropriate in a high demand, resource limited healthcare setting.

## Data Availability

Not applicable.

## Abbreviations

AE: Adverse event
AR: Adverse reaction
BOR: Best objective response
BRAF: A human gene that encodes a protein called B-Raf
CI: Confidence interval
CR: Complete response
CRF: Case report form
CT: Computerised tomography
CTCAE v5.0: Common Toxicity Criteria for Adverse Events version 5
CTLA-4: Cytotoxic T-lymphocyte-associated antigen 4
CTRU: Clinical Trials Research Unit
DANTE: A randomised phase III study to evaluate the Duration of ANti-PD-1 monoclonal antibody Treatment in patients with metastatic mElanoma
DMEC: Data Monitoring and Ethics Committee
ECOG: Eastern Cooperative Oncology Group
EORTC: European Organisation for Research and Treatment of Cancer
GCP: Good Clinical Practice
HEAP: Health economics analysis plan
HIV: Human immunodeficiency virus
HR: Hazard ratio
ICER: Incremental cost effectiveness ratio
ITT: Intention to treat
MAR: Missing at random
MAP: Mitogen activated protein
MEK: Mitogen activated protein kinase
MRI: Magnetic resonance imaging
NCRI: National Cancer Research Institute
NHS: National Health Service
NICE: The National Institute for Health and Care Excellence
NIHR: National Institute for Health Research
NMB: Net monetary benefit
OS: Overall survival
PD: Progressive disease
PD-1: Programmed cell death protein 1
PDL-1: Programmed cell death ligand 1
PET: Positron emission tomography
PFS: Progression-free survival
PR: Partial response
QALYs: Quality adjusted life years
QoL: Quality of life
REC: Research ethics committee
RECIST v1.1: Response Evaluation Criteria In Solid Tumours version 1.1
SAR: Serious adverse reaction
SD: Stable disease
SUSAR: Suspected unexpected serious adverse reaction
TSC: Trial Steering Committee
UK: United Kingdom
